### 3. Rationale

In the light of the current information on SARS-CoV 2 pathogenesis, we speculate that the majority of SARS-CoV 2- infected patients are capable of clearing the virus by means of their effective endogenous IFN-I system and do not require hospitalization. We assume that in a minority of people a defective IFN-I system may favor SARS-CoV 2 spread, eventually causing the development of severe forms of COVID-19 and dismal prognosis. People aged >65 years, for which an impairment of IFN-I induction in response to viral infection has been documented (16,36,37), are at higher risk of severe COVID-19 (38).

In these patients, a delayed IFN-I response and the loss of viral control might contribute in early phases of infection to disease outcome. Data suggest that the IFN- $\beta$  subtype appears to be the most suited for COVID-19 treatment (39). Thus, we hypothesize that elderly patients will greatly benefit from a short term IFN-I administration at the earliest time of SARS-CoV 2 infection, thus compensating the insufficient or impaired endogenous IFN-I production and preventing COVID-19 progression to severe forms of disease. In light of its immunomodulatory properties, IFN- $\beta$  administered at the early phases of infection can represent a valuable tool to enhance humoral and cellular immunity in addition to its direct antiviral treatment restricting early viral spread, thus halting virus replication and preventing the progression towards severe forms of disease.

### 4. Impact for the National Health System

Italy was the first European country to experience COVID-19 pandemic, when the information about viral pathogenesis and therapeutic options were scarcely available. Moreover, Italian demographic structure, with a high percentage of population above 65 years of age, greatly affected the outcome and the death toll of the first epidemic wave. In fact, data show that not only sex and comorbidities, but also age increases the risk of developing severe COVID-19 (38,40) needing hospitalization and intensive care support. Since the first case, recorded in Italy on February 21th, COVID-19 represented a big challenge for the Italian National Health System, which underwent an increasing pressure until

[figure not shown]

restriction measures were undertaken to avoid its collapse. However, the interruption of non-essential economic and social activities has a serious impact on global economy and people quality of life in the long term. For elderly people, isolation can result not only in increased risks of cardiovascular, autoimmune and neurocognitive disorders, but also induce or exacerbate mental health problems, such as depression and anxiety. The introduction of a new phase, in which the restriction measures were gradually released and economic activities restarted, required some strategies to be undertaken to keep an acceptable risk for all population. A reinforced surveillance system was developed and is currently in use to ensure a prompt diagnosis of new cases. Nevertheless, it is urgent to develop and test new treatment options that can be administered during the early infection to reduce viral shedding, and consequent contagion, and to hamper disease progression toward severe forms, thus diminishing the impact on the National Health System.

In this trial, particular attention is given to aged patients with a recent diagnosis of COVID-19 in the presence of mild symptoms. In these patients, a strict medical control during home isolation, or a precautionary hospitalization are both appropriate choices, to monitor the possible rapid evolution of the infection. However, no therapeutic regimen specifically designed for these patients is available. Therefore, the risk of developing severe forms of the disease requiring intensive care or ending in fatalities is still high.

This trial will test the efficacy of IFN- $\beta$  administered to aged patients during the early phase of the infection, in limiting viral replication and preventing the evolution of COVID-19 towards severe and critical diseases. Individual infectivity is directly associated with disease severity and time of viral shedding. Moreover, preventing severe COVID-19 will directly reduce lethality and will immediately mitigate the hospitals overworking, thus overall reducing the potential impact of COVID-19 on the National Health System.

## 5. Objectives of the study

This trial aims at exploring the use of IFN- $\beta$ 1a in SARS-CoV 2 newly diagnosed elderly patients with increased risk of developing severe COVID-19. In particular, this study will evaluate low-dose and discontinuous use of IFN- $\beta$ 1a in the early phase of infection, in order to exploit not only its antiviral,

[figure not shown]

but also its immune activating and anti-inflammatory properties. Such regimen should avoid any toxicity and refractoriness phenomena often occurring during IFN-I chronic administration.

## 5.1 Primary Objective

Primary Objective of the study is to evaluate the reduction in disease progression in patients treated with IFN versus control group within 28 days.

### 5.1.1 Primary endpoint and outcome

Primary endpoint of the study is the proportion of patients experiencing a disease progression, during at least 5 days, according to the National Early Warning Score (**NEWS2**). The **NEWS2** score is a standardized approach aimed at promptly detecting signs of clinical deterioration in acutely ill patients and establishing the potential need for higher level of care. It is based on the evaluation of vital signs including respiratory rate, oxygen saturation, temperature, blood pressure, pulse/heart rate, AVPU response. The resulting observations, compared to a normal range, are combined in a single composite “alarm” score. Any other clinical sign clearly indicating a disease worsening will be considered as disease progression.

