**Chart 1: The NEWS scoring system**

| Physiological parameter        | 3           | 2      | 1         | Score 0                   | 1               | 2               | 3                   |
|--------------------------------|-------------|--------|-----------|---------------------------|-----------------|-----------------|---------------------|
| Respiration rate (per minute)  | $\leq 8$    |        | 9–11      | 12–20                     |                 | 21–24           | $\geq 25$           |
| SpO 2 Scale 1 (%)   | $\leq 91$   | 92–93  | 94–95     | $\geq 96$                 |                 |                 |                     |
| SpO 2 Scale 2 (%)   | $\leq 83$   | 84–85  | 86–87     | 88–92
$\geq 93$ on air | 93–94 on oxygen | 95–96 on oxygen | $\geq 97$ on oxygen |
| Air or oxygen?                 |             | Oxygen |           | Air                       |                 |                 |                     |
| Systolic blood pressure (mmHg) | $\leq 90$   | 91–100 | 101–110   | 111–219                   |                 |                 | $\geq 220$          |
| Pulse (per minute)             | $\leq 40$   |        | 41–50     | 51–90                     | 91–110          | 111–130         | $\geq 131$          |
| Consciousness                  |             |        |           | Alert                     |                 |                 | CVPU                |
| Temperature (°C)               | $\leq 35.0$ |        | 35.1–36.0 | 36.1–38.0                 | 38.1–39.0       | $\geq 39.1$     |                     |

For non-hospitalized patients, measurements will be auto-performed by the patient either assessed by a caregiver or a family member. Training on how to use the provided devices will be performed by USCAR unit at T1, written instructions will be also provided, and additional help will be given

[figure not shown]

upon request by phone or videocall. Measurements will be recorded on the clinical diary that will be provided (Appendix 5). Patients will be contacted daily by USCAR dedicated unit and will communicate by phone their health status that will be registered on a dedicated clinical records form (Appendix 5). USCAR unit approaching COVID-19 patients will use personal protective equipment including a FFP3 (or FFP2) mask, gloves, gown and goggles. FFP3 will be used always in case of any procedure on respiratory tract (including nasopharyngeal swab).

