### 9.2 Blinding

This is an open-label study. After the randomization, patient will be notified whether will receive or not the experimental drug.

[figure not shown]

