## 10. Statistical Plan

The primary analysis will be carried out on the primary endpoint on the intention-to-treat (ITT) population defined as all patients randomized receiving at least one dose of treatment.

The percentage of patients undergoing disease progression defined on rate of progression of NEWS2 score lasting more than 5 days will be calculated in two arms (IFN- $\beta$ 1a + standard of care vs standard of care) of the trial. For persons who died, a conservative approach will be adopted and death will be considered an event. The effect of treatment will be estimated through a logistic regression model including a dummy variable for treatment. The effect of treatment will be estimated through multivariable logistic regression model by accounting for the following

[figure not shown]

covariates: age, gender, co-morbidities. Moreover, NEWS2 score at baseline and setting of recruitment will be also considered.

All primary and secondary analyses will be carried out both on ITT population and on per-protocol population. Per-protocol population includes all subjects who were included in the ITT population that received the treatment as defined in the protocol and who completed the study with no major protocol violations.

Kaplan-Meier survival analysis and Cox proportional hazards model will be used for time-to-event data. The following covariates will be included in the Cox model: age, gender, co-morbidities. Moreover, NEWS2 score at baseline and setting of recruitment will be also considered. For the secondary endpoint ICU-free days, a competing risk model will be adopted considering death a competing event, following the method proposed by Fine and Gray (57). Moreover, the median difference will be reported.

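### Section 5.1.1 adds an open-ended clinical judgement to the primary endpoint of an open-label trial, and Sections 5.4 and 10 do not count it

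*Protocol*

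**What the plan says.** - **Section 5.1.1** sets the primary endpoint as the "proportion of patients experiencing a disease progression, during at least 5 days, according to the National Early Warning Score". It ends with a second route to an event: "Any other clinical sign clearly indicating a disease worsening will be considered as disease progression". The only limit is that the sign must point clearly to worsening. No signs are listed, nobody is named to judge them, and the sentence states no duration.
- **Section 5.4** powers the trial on NEWS2 progression lasting more than 5 days and does not mention other signs.
- **Section 10** analyses progression "defined on rate of progression of NEWS2 score lasting more than 5 days" and adds for patients who die that "death will be considered an event". It does not mention other signs either.
- **Section 9.2:** "This is an open-label study", and after randomization the "patient will be notified whether will receive or not the experimental drug". Under Section 8.2 the control arm receives standard of care without placebo. No blinded or independent review of progression events appears in the protocol.
- **Section 8.3:** outside hospital, "measurements will be auto-performed by the patient either assessed by a caregiver or a family member", and patients report their status by telephone each day.
- **Section 9.4.1** lists influenza-like symptoms and headache as very common with the drug, and myalgia, arthralgia, fatigue and fever as common. Table 3 of Appendix 4 lists headache, muscle aches, joint pain, fatigue and fever history among the signs and symptoms to be recorded.

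**The concern.** The sections that state the primary event do not agree. An analyst following 5.1.1 counts patients whom an analyst following Section 10 does not. This is not a detail left for later: the protocol fixes the event twice, with different content.

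The extra route is also the part of the endpoint most open to influence. NEWS2 rests on measured vital signs and must persist. A further sign of worsening rests on judgement, and here everyone involved knows the arm. Two pressures act in opposite directions:

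- untreated controls may be called worse more readily, which favours interferon;
- drug reactions that resemble COVID-19 symptoms may be called worsening, which counts against interferon.

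With 20 controls and 40 treated patients, a few reclassified patients can change the result.

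**Working it through.** **Step 1. Reproduce the plan's sample size.** Inputs from Section 5.4: control 0.50, interferon 0.15, two-sided 5%, power 80%, allocation 2:1. The pooled rate is (0.50 + 2 × 0.15)/3 = 0.2667. Fleiss without continuity correction, per control arm:

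n = [1.960 × √(1.5 × 0.2667 × 0.7333) + 0.8416 × √(0.50 × 0.50 + 0.15 × 0.85/2)]² / 0.35²

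= (1.0615 + 0.4714)² / 0.1225 = 19.2, rounded up to 20 controls and 40 treated, 60 in total. This matches the plan. Exact enumeration of the two binomials with the uncorrected pooled z-test (two-sided 5%) gives power 82%.

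**Step 2. Model the clause.** Let q be the share of patients without NEWS2 progression whom the clause turns into events. The observed rate becomes p + (1 − p)q. The protocol gives no value for q; 10% and 20% are assumptions.

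**Step 3. No true effect, over-calling in controls only.** Same exact enumeration, 20 versus 40:

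| True rate, both arms | Observed control rate, q = 10% / 20% | Two-sided false-positive rate, q = 0 | q = 10% | q = 20% |
|---|---|---|---|---|
| 0.15 | 0.235 / 0.32 | 4.4% | 13.0% | 33.5% |
| 0.30 | 0.37 / 0.44 | 5.1% | 8.9% | 19.3% |
| 0.50 (the plan's control rate) | 0.55 / 0.60 | 5.5% | 7.0% | 11.9% |

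For example, 0.15 + 0.85 × 0.10 = 0.235. Almost all of the excess favours interferon: at a true rate of 0.15, false results in its favour go from 2.5% to 12.7% (q = 10%) and 33.5% (q = 20%). Fisher's exact test shows the same pattern at lower levels: 10.3% and 27.2% two-sided in the first row.

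**Step 4. The planned effect is real, 0.50 versus 0.15.**

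| Over-calling of 10% | Control | Interferon | Power |
|---|---|---|---|
| none | 0.50 | 0.15 | 82% |
| interferon arm only | 0.50 | 0.15 + 0.85 × 0.10 = 0.235 | 54% |
| both arms | 0.50 + 0.50 × 0.10 = 0.55 | 0.235 | 68% |

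**Step 5. What can be recovered.** Appendix 2 schedules NEWS2 every day, and the case report form in Appendix 4 stores the score with its vital signs, so a NEWS2-only event can be derived whatever was judged on other signs. The judged events are less well documented. The form has no field for a progression event or its reason. The follow-up pages for days 11–13 and 15–27 omit signs and symptoms, although Appendix 2 schedules them daily.

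**The case against.** The strongest reply is that Section 10 governs the analysis. On that reading other signs never reach the primary test and the inflation is zero. This stands as a reading, and it is why the figures above are conditional. It does not remove the contradiction, because 5.1.1 is the section that defines the endpoint.

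Second, the control-only scenario is one choice among several. The over-call rates have no source in the protocol, the largest figures belong to a 15% base rate, and at the plan's own 50% the rise is modest. Equal over-calling leaves the false-positive rate near 5% and costs only power. All of this is right. The planned analysis is also logistic regression with covariates, and the adjusted model was not examined.

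A reader might draw four stronger conclusions that the text does not support:

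- **That the criterion is unlimited.** The sign must clearly indicate worsening. This is a weak limit, but it is one.
- **That patients decide who has progressed.** Section 8.3 has them measure vital signs and report by telephone; Section 12 gives clinical monitoring of home patients to trained physicians. No section says who classifies progression.
- **That the clause certainly bypasses the 5-day rule.** The sentence extends the same term, disease progression, to which the duration is attached, so the duration may be meant to carry over. The text is ambiguous.
- **That the damage could not be undone.** The daily NEWS2 scores allow a NEWS2-only analysis.

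A list of signs or an adjudication procedure might sit in a statistical analysis plan. That would not settle which of two conflicting protocol definitions holds.

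**Conclusion.** The point holds as an internal contradiction on the primary event, with a risk of bias if 5.1.1 is followed. What is certain from the text: 5.1.1 admits judged signs without list, assessor or stated duration; 5.4 and 10 do not count them; and the trial is open label without placebo.

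What is conditional is the size. It assumes that the clause is applied and that 10% to 20% of non-progressors are over-called. On those assumptions a true null gives a two-sided false-positive rate between 7% and 33%, depending on base rate and q. A real effect of the planned size loses power to 54% or 68% when q is 10%. The direction cannot be predicted, so it would be wrong to say that the clause creates an apparent benefit of interferon. It should be settled before any comparison of outcomes by arm, because it decides which patients count in the primary result.

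**What to change.** Remove the sentence from the primary endpoint definition in 5.1.1. If events beyond NEWS2 should count, replace it with a closed list of objective, dated events, worded identically in 5.1.1, 5.4 and 10. Use one duration wording at the same time, since 5.1.1 says at least 5 days and the other two say more than 5.

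Death is already an event in Section 10. ICU admission is already captured under Section 8.5, although that section words it for progressing patients; if it becomes a primary event, state that it is recorded for everyone. If the start of oxygen is listed, add an explicit dated field, because the NEWS2 items in the case report form design include saturation but no oxygen field. Report other investigator-judged worsening as a supportive outcome only.

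The costs are a formal amendment under Section 13.2, and some genuine short-lived deteriorations that no longer count as primary events. Removing the sentence leaves the sample size calculation at 60. Decisions on oxygen and ICU admission are still made by unblinded clinicians, so a list that includes them reduces the bias without removing it.

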## 5.2 Secondary Objectives and Endpoints

The following table 1 contains the secondary objectives and endpoint of the study

| Objective                                                                                                                                                  | Endpoint                                                                                                           |
|------------------------------------------------------------------------------------------------------------------------------------------------------------|--------------------------------------------------------------------------------------------------------------------|
| 1) To assess the reduction in ICU admission in patients treated with IFN versus control group within 28 days of randomization                              | ICU-free days at 28 days (Day 1 through Day 28)                                                                    |
| 2) To assess the reduction in number of deaths in IFN compared to control group (day 28)                                                                   | All-cause mortality (Day 1 through Day 28)                                                                         |
| 3) To evaluate the increase in proportion of participants returning to negative SARS-CoV 2 RT-PCR in IFN-treated versus control group at Day 14 and Day 28 | Negative SARS-CoV 2 RT-PCR at day 14 post-randomization
Negative SARS-CoV 2 RT-PCR at day 28 post-randomization |

|                                                                                                                    |                                                                                      |
|--------------------------------------------------------------------------------------------------------------------|--------------------------------------------------------------------------------------|
| 4) To assess the increase in SARS-CoV 2-Specific Binding Antibody Titers in IFN compared to control group (day 28) | Change from Baseline in SARS-CoV 2-Specific Binding Antibody Titers at day 14 and 28 |
| 5) To assess the safety of IFN-treated patients versus control group                                               | Incidence of adverse events                                                          |

For secondary endpoints, more detailed descriptions follow:

- 1) ICU-free days at 28 days will be calculated as the number of days a patient is not in an ICU. Time Frame will be: Admission (day 0) to 28 days after admission (day 28). In case of death, it will be counted as 0 day;
- 2) All-cause mortality will be: total number of death events occurring within day 0 and day 28;
- 3) Negative SARS-CoV 2 RT-PCR is defined as an undetectable presence of SARS-CoV 2 genes, as determined by PCR on an adequate sampling of upper respiratory tract.
- 4) Change from Baseline in SARS-CoV 2-Specific Binding Antibody Titers is defined as the difference in anti-SARS-CoV 2-specific antibody levels measured at day 28 versus day 0;
- 5) Details on safety event are described in paragraph 9.4

### 5.3 Exploratory Endpoints

Exploratory studies will be also performed on blood samples collected before and after treatment to assess:

- IFN-I signaling activation
- Cellular immune monitoring
- Systemic inflammatory markers

#### 5.3.1 IFN-I Signaling

Pioneer studies in animal models showed that the complete absence of IFN-I signalling, by deletion of IFN-I receptor, enhanced mice susceptibility and mortality from several viral infections (7). IFN-I signalling downregulation may occur during viral infections as a consequence of viral-specific evasion mechanisms that Coronaviruses mainly establish during the early phase of infection (29,31). Diminished levels of IFN-I or Interferon Stimulated Genes (ISG) expression have been detected in the peripheral blood mononuclear cells of SARS and MERS patients (32,33). More relevantly, the

[figure not shown]

results of a very recent work clearly showed an impaired IFN-I signaling, associated with persistent blood virus load and an exacerbated inflammatory response in patients with severe COVID-19 (35). A diminished level of endogenous IFN-I activation and signalling may also occur as a consequence of aging, as reported in several *in vitro* and *in vivo* settings (17,41). In light of these considerations, the level of expression of selected ISG will be analysed in patients PBMC as surrogate markers of IFN-I signalling activation. Samples will be collected before, during and after the completion of IFN- $\beta$ 1a treatment in order to assess 1) possible correlations between IFN-I activation status and patient clinical outcome *per se*; 2) treatment-induced modifications of IFN-I signalling activation possibly associated with clinical improvement.

#### 5.3.2 Cellular Immune-Monitoring

A decrease in peripheral lymphocyte count (with lower frequencies and absolute counts of CD3, CD4, CD8 T cells as well as of NK subsets) and an inflammatory cytokine storm may be the main reasons for rapid disease progression and poor treatment response in severe COVID-19. The neutrophil-to-CD8+ T cell ratio and the neutrophil-to-lymphocyte ratio were identified as prognostic factors affecting the prognosis for severe COVID-19 (42). Besides quantitative alteration, T cell maturation status was found to be modified since the percentage of naïve helper T cells increases and memory helper T cells decreases in severe cases. Patients with COVID-19 have also low levels of regulatory T cells, showing damaged features in severe cases (43). In general, COVID-19 patients show marked T cell activation, senescence, exhaustion and skewing towards Th17, if compared to healthy subjects (44).

The innovative technology MFC will help in elucidating the immunomodulatory *in vivo* effect of IFN  $\beta$ 1a treatment. Leukocyte subpopulation frequency, activation status and functionality will be explored in pre- and post-treatment patients' blood samples. MFC results will be correlated with clinical outcome in order to identify potential peripheral immune markers of response to treatment.

